## Abstract

**Background**: Chronic low back pain (CLBP) is a common musculoskeletal disorder that significantly impairs quality of life and is frequently associated with vitamin D deficiency. Therapeutic exercise is a cornerstone of management, yet the optimal adjunct intervention to restore serum vitamin D levels remains uncertain. No prior randomized trial has compared oral vitamin D supplementation with lifestyle education on sun exposure, nutrition, and physical activity, both combined with therapeutic exercise. We hypothesize that therapeutic exercise plus an education booklet (TEB) may be superior to therapeutic exercise plus oral vitamin D supplementation (TED) in reducing pain and disability while improving serum vitamin D levels.

**Methods**: This assessor-blinded, two-arm, multicenter randomized controlled trial (RCT) will be conducted in hospitals and rehabilitation centers in Dhaka city, Bangladesh. Adult participants (18–65 years) with CLBP and confirmed vitamin D deficiency will be recruited and randomized to either TEB or TED groups. Both groups will receive standardized therapeutic exercise protocols. The intervention duration will be 6 months, with assessments at baseline, 2 months, and 6 months. Primary outcomes include pain intensity measured by the Brief Pain Inventory (BPI) and serum 25(OH)D3 levels. Secondary outcomes include disability assessed by the Roland-Morris Disability Questionnaire (RMDQ). Statistical analysis will follow the intention-to-treat principle, using repeated measures ANOVA to compare group differences over time.

**Discussion**: This trial will provide evidence on whether a multidimensional lifestyle-based education approach combined with therapeutic exercise offers greater benefit than vitamin D supplementation with exercise in CLBP patients with vitamin D deficiency. The findings will inform clinical guidelines and support comprehensive management strategies for CLBP, particularly in resource-limited settings.

Registration: Clinical Trials Registry India (
CTRI/2022/11/047074).

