### Randomization

Researchers plan for hospital-based randomization in both study centers from 1
^st^ December 2022 to 30
^th^ May 2023 by sequential random sampling and eligibility screening. Participants were randomly assigned to either the therapeutic exercise plus education booklet (TEB) group or the therapeutic exercise plus vitamin D3 supplementation (TED) group using a computer-generated randomization sequence. Randomization was stratified by study center to ensure balanced distribution across sites. Allocation concealment was maintained through the use of sequentially numbered, opaque, sealed envelopes prepared by an independent researcher not involved in recruitment or assessment.

Blinding was implemented at multiple levels to minimize bias. Outcome assessors were blinded to group allocation throughout the study, ensuring objective evaluation of pain, disability, and serum vitamin D levels. Data analysts were also blinded to group identity during statistical analysis. Due to the nature of the interventions, participants and treating physiotherapists could not be blinded; however, strict separation between intervention delivery and outcome assessment was maintained to preserve methodological rigor.

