### Data analysis

Data will be analyzed based on its nature. Calculation and data auditing will be done using Microsoft Excel 2016. Data will be analyzed by SPSS version 23, and R-4.2.1 for Windows. Eligibility for parametric analysis will be checked using bell’s curve, skewness, kurtosis, Kolmogorov–Smirnov test and Shapiro–Wilk test. Continuous variables will be represented by using an arithmetic mean and standard deviation. Categorical data will be represented by percentage (%) and frequency. Baseline characteristics between groups will be compared using chi-square tests for categorical variables and independent t-tests or Mann–Whitney U tests for continuous variables, depending on data distribution. Normality will be assessed using the Shapiro–Wilk test. For within-group comparisons across time points (baseline, 2 months, and 6 months), repeated measures ANOVA will be applied for parametric data, with Greenhouse–Geisser correction if sphericity is violated; the Friedman test will be used for non-parametric data. Between-group differences over time will be analyzed using mixed-model repeated measures ANOVA, which accounts for group × time interactions, or generalized estimating equations (GEE) if assumptions are not met. Post-hoc pairwise comparisons will be adjusted using Bonferroni correction. Effect sizes (Cohen’s d or partial eta squared) will be reported to indicate the magnitude of differences. All analyses will be conducted at a two-tailed alpha level of 0.05, and intention-to-treat principles will be applied to handle missing data.

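### Intention-to-treat is named as the missing-data method, and the repeated-measures ANOVA may keep complete cases only and makes less use of baseline than an adjusted mixed model would

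*Protocol article*

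**What the plan says.** The Abstract says: "Statistical analysis will follow the intention-to-treat principle, using repeated measures ANOVA to compare group differences over time".

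The Data analysis section says: "Between-group differences over time will be analyzed using mixed-model repeated measures ANOVA". That model is to cover the interaction of group with time, and the stated fallback is "or generalized estimating equations (GEE) if assumptions are not met". On missing values its only statement is that "intention-to-treat principles will be applied to handle missing data".

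Baseline is listed as a time level for the within-group analysis: "For within-group comparisons across time points (baseline, 2 months, and 6 months), repeated measures ANOVA will be applied for parametric data". The Greenhouse–Geisser correction is attached to that within-group sentence. For the between-group analysis, the time levels are not listed and no baseline covariate or centre term is mentioned. Post-hoc pairwise comparisons are Bonferroni-adjusted, and either Cohen's d or partial eta squared is to be reported.

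The Randomization section says: "Randomization was stratified by study center to ensure balanced distribution across sites". The Study setting section delivers the booklet arm at one centre and the vitamin D arm at the other.

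**The concern.** Three things need correcting.

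1. **Missing data.** A missing-data method is named, and it is not one. Analysing everyone as randomised leaves open what to do with an absent 2- or 6-month value.
2. **The model label.** A classical split-plot ANOVA deletes any patient with a missing visit, and is biased if dropout depends on earlier response. A likelihood mixed model keeps partial data under missing at random. The GEE fallback also keeps partial data, but without weighting it generally needs data missing completely at random. The plan can therefore move between different analysed patients and different missing-data assumptions, and the switch to GEE is decided by assumption checks on the trial's own data.
3. **The contrast.** With baseline as one of three time levels, group × time is a 2-df test. The 2- and 6-month contrasts inside it are differences in change from baseline. No single visit is marked as the primary comparison, and the baseline value is used less efficiently than it could be.

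At stake are possible bias from discarded patients, lost precision on data already collected, and the lack of one designated treatment effect with its confidence interval.

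**Working it through.** **The plan's own figure.** The Sample size section gives a minimum of 152 in total, two-sided alpha 0.05 and power 80%, with no effect size or SD, so 152 cannot be reproduced forwards. Solved backwards with 76 per arm (1:1 assumed), the normal formula gives d = (1.960 + 0.842) × √(2/76) = 0.4545 SD. The t-test version gives 0.457 SD, which is used below.

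**Loss of patients under a classical ANOVA.** No dropout rate is given. Assume 10% missing at 2 months and 20% at 6 months.
- Independent missingness: 0.90 × 0.80 = 0.72 complete; 0.72 × 152 = 109 kept, 28% lost.
- Monotone dropout (those missing at 2 months are also missing at 6): 0.80 × 152 = 122 kept, 20% lost.

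The loss comes from complete-case deletion, not from treating baseline as an outcome. In one simulated data set of 152 with monotone dropout at about these rates, listwise deletion kept 122 patients. A mixed model with baseline as a time level kept 152. A mixed model of post-baseline values with baseline as a covariate kept 137, because 15 had no follow-up.

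**Precision at one visit.** Assume SD = 1 at each visit and correlation r between baseline and follow-up.
- Change from baseline: variance 2(1 − r).
- Baseline-adjusted: variance 1 − r².
- Ratio: 2(1 − r)/[(1 − r)(1 + r)] = 2/(1 + r).

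Power = Φ(0.457/√(v × 2/76) − 1.96), where v is the variance above and √(2/76) = 0.1622:

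| r | v, change | v, adjusted | Ratio | Power, change | Power, adjusted |
|---|---|---|---|---|---|
| 0.3 | 1.40 | 0.91 | 1.54 | 66% | 84% |
| 0.5 | 1.00 | 0.75 | 1.33 | 80% | 90% |
| 0.7 | 0.60 | 0.51 | 1.18 | 95% | 98% |
| 0.8 | 0.40 | 0.36 | 1.11 | 99% | 100% (99.7%) |

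Worked line at r = 0.5: 0.457/0.1622 = 2.817, and 2.817 − 1.96 = 0.857, giving 80%. Adjusted: 2.817/√0.75 = 3.253, and 3.253 − 1.96 = 1.293, giving 90%.

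**Centre.** If each arm is delivered at its own centre, as Study setting says, the design matrix with intercept, arm and centre has rank 2 of 3, so the arm effect cannot be estimated with centre in the model. If both arms run at both centres, as stratification by centre implies, the rank is 3 and a centre term is possible.

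**The case against.** **Complete-case deletion is inferred, not stated.** This stands. The Data analysis section says mixed-model, which can mean a likelihood model, and its GEE fallback uses all available visits. The Greenhouse–Geisser correction belongs to the within-group sentence, and partial eta squared is only one of two options. Against this, the Abstract promises plain repeated-measures ANOVA, a two-group split-plot ANOVA is commonly called mixed, and a fallback when assumptions fail suits a classical method better. A reader might infer that the plan certainly drops every incomplete patient and so contradicts its own intention-to-treat claim. The text supports only that this is the likelier reading.

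**The power gain depends on assumptions.** This also stands. The article gives no r, and at r = 0.7 or above the gain is small. A reader might be tempted to set the 2-df interaction test against an adjusted 6-month contrast to show a larger loss, but that mixes the choice of visit with baseline adjustment. The Interventions section gives exercise and vitamin D for 8 weeks, so an effect peaking at 2 months is plausible. With the full 0.457 SD at 2 months and half of it at 6, the adjusted 6-month contrast has only 37% power at r = 0.5. The fair comparison is the same contrast with and without adjustment.

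**Model detail belongs in an analysis plan, and group × time with pairwise comparisons does address 2 and 6 months.** This is partly right. The absence of covariates or a covariance structure from an article is not in itself an error. But naming intention-to-treat as the missing-data method is a misstatement, and the two method labels admit analyses of different patients.

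**Attrition is planned for.** Sample size does mention extra recruitment, without a number. That could protect power, but not against bias from deleting incomplete patients.

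**Conclusion.** The point holds in limited form and is worth acting on. The misstatement about intention-to-treat is certain. The complete-case loss is conditional on the classical reading, and its size of about 20% to 28% rests on assumed visit losses. The variance penalty of 2/(1 + r) applies if baseline is a time level in the between-group analysis, which is the natural reading. It assumes equal SDs at baseline and follow-up. In power terms it is about 10 points at r = 0.5 and 2 at r = 0.7.

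A reader might infer that a baseline-adjusted mixed model settles every difficulty here. It does not:
- A centre term stays inestimable while each arm has its own centre.
- A model of follow-up values alone loses patients with no follow-up.
- Missing at random remains an assumption.
- The Eligibility criteria list withdrawal during the 8 weeks as an exclusion, while the Interventions section keeps the data of patients who stop. That conflict over the analysed population is separate, and no choice of model removes it.

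**What to change.** 1. Delete the statement that intention-to-treat handles missing data. Say that all randomised patients are analysed in their assigned arm, that missing values are assumed missing at random given the observed data, and that a sensitivity analysis (for example, delta-adjusted) tests that assumption.
2. For each continuous outcome, state one REML mixed model with arm × visit and an unstructured covariance. Adjust for baseline either by a common (constrained) baseline mean across arms, which also keeps patients with no follow-up, or by a baseline × visit covariate, which does not.
3. Name the primary visit in advance and report the adjusted arm difference there with its 95% confidence interval.
4. Drop the switch to GEE that depends on assumption checks. Robust standard errors, or log 25(OH)D, can serve as sensitivity analyses.
5. Use the same method label in the Abstract and in Data analysis.
6. Reconcile Study setting with Randomization first; add centre to the model only if both arms run at both centres.

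Items 1 to 5 change wording only, and SPSS and R, both already named, fit the model. Item 6 needs at least a clarification of where each arm is treated, and a design change if each arm really is confined to one centre.

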Chronic low back pain (CLBP) has been associated with vitamin D deficiency, which affects calcium metabolism, bone health, and muscle function. Deficiency may lead to osteomalacia, muscle weakness, and impaired neuromuscular control, increasing spinal instability and pain. Additionally, low vitamin D levels can elevate pro-inflammatory cytokines, intensifying pain sensitivity and contributing to chronic musculoskeletal disorders.
^
8
^ Clinical studies have reported a higher prevalence of vitamin D deficiency among patients with CLBP compared to healthy controls, suggesting a potential association between deficiency and pain severity.
^
17,
18
^ Vitamin D supplementation has been explored as a supportive measure in CLBP due to its role in bone health, muscle strength, and inflammation regulation.
^
19
^ Correcting deficiency may improve musculoskeletal function and reduce pain sensitivity, with clinical trials reporting symptomatic improvement in deficient patients.
^
20,
21
^ However, meta-analyses indicate limited overall efficacy, suggesting benefits may be restricted to those with confirmed deficiency, while excessive intake carries risks such as hypercalcemia and kidney stones.
^
22
^

This study hypothesizes that multidimensional comprehensive management through therapeutic exercise combined with an education booklet on sun exposure, nutrition, and lifestyle (TEB) will be superior to therapeutic exercise with oral vitamin D supplementation (TED) in patients with chronic low back pain and vitamin D deficiency. Specifically, it is expected that participants in the TEB group will demonstrate greater improvements in pain symptoms, serum vitamin D levels, and disability status compared to those in the TED group, with these effects observed at both 2 and 6 months following baseline recruitment. Following the study hypothesis, this trial holds clear clinical significance: for clinicians, it offers evidence to guide treatment choices between exercise combined with education or vitamin D3; for patients, it evaluates accessible, low-cost strategies that may improve pain and function; and for researchers, it provides rigorous comparative data to inform future studies on scalable interventions for CLBP.

The specific objectives are:

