## Discussion

There is an increasing concern of LBP and vitamin D deficiency for chronic pain suffers that is leading the working people towards disability and inefficiency to work.
^
5
^
^,^
^
9
^ A non-randomized quasi experimental study
^
10
^ found therapeutic exercise and vitamin D oral supplementation is effective to reduce pain, replenish vitamin D3 level with short term results. Our study will meet the necessity of randomized systematic evaluation of therapeutic exercises and vitamin D supplement compensation in two different approaches, either by sun exposure, nutrition and healthy lifestyle or by taking oral supplements. We will evaluate outcome in both short term (2 months) and long-term effect after 6 months of stopping the intervention. The experimental group is the therapeutic exercise and booklet group because we assume a positive lifestyle and exercise can replace the role of oral medication supplement, as these were derived as a predictor in observational studies.
^
9
^

The methodological standard of the proposed trial adheres to the Enhancing the QUAlity and Transparency Of health Research (EQUATOR) guidelines to ensure the rigor of the study. As this is a two tailed hypothesis, we assume any treatment can be superior or both may have similar effect. The similar effect is also a positive finding, because oral vitamin D supplement have some adverse effects if taken for longer durations.
^
12
^ Moreover, if the study would have four arms including two interventions, a group with only vitamin D supplement and another with therapeutic exercise and a placebo vitamin D supplement, that could ensure true effects. However, researchers had to limit the study considering funding, scope of practice and complicated management issues. As outcome indicators pain and vitamin D3 levels will be used as primary outcomes and disability as secondary outcome, because previous research suggests disability as a consequence.
^
36
^ BPI measures not only pain severity, but also pain affective interference and pain physical interference,
^
10
^
^,^
^
30
^ that is consistent to the effect of intervention.

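### The planned group × time interaction test has no direction and no visit, so alone it cannot establish that TEB is better at both 2 and 6 months

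*Protocol article*

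**What the plan says.** The Introduction of the protocol article states the hypothesis with a direction, "participants in the TEB group will demonstrate greater improvements in pain symptoms, serum vitamin D levels, and disability status", and with a time requirement, "with these effects observed at both 2 and 6 months following baseline recruitment".

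The Data analysis section gives the between-group method: "Between-group differences over time will be analyzed using mixed-model repeated measures ANOVA, which accounts for group × time interactions", with GEE as the alternative if assumptions fail. The Abstract is briefer: "using repeated measures ANOVA to compare group differences over time". The other relevant provisions of the Data analysis section are:

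- Level: "All analyses will be conducted at a two-tailed alpha level of 0.05".
- Follow-up tests: "Post-hoc pairwise comparisons will be adjusted using Bonferroni correction". Which pairs, and how many, is not stated.
- Effect size: "Effect sizes (Cohen’s d or partial eta squared) will be reported to indicate the magnitude of differences".

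The Discussion describes the hypothesis differently: "As this is a two tailed hypothesis, we assume any treatment can be superior or both may have similar effect".

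The article names no between-group contrast at 2 or 6 months, and no rule for what counts as success at both.

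**The concern.** The hypothesis is a signed, joint claim about two visits. The published test asks whether the two arms' three-visit profiles are parallel. Any real departure in shape can reject that null: benefit at one visit only, TED better throughout, or a reversal between visits.

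A visit-dependent pattern is foreseeable for serum 25(OH)D, a primary outcome. The TED capsules run for 8 weeks and the second blood sample is taken as that treatment ends, whereas the booklet advice could act for longer.

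At stake is how a significant interaction would be read. If it were taken as support for the stated hypothesis, the conclusion would rest on a statistic that looks the same whichever arm did better. When the hypothesis is true, an omnibus test followed by Bonferroni-adjusted visit tests is also a less powerful route to the claim than testing it directly.

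**Working it through.** **Inputs from the protocol article.** Three visits (baseline, 2 and 6 months); two-sided alpha 0.05; a minimum of 152 participants; 80% power.

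**Inputs assumed, because the article does not give them.** 1:1 allocation (n = 76 per arm), SD 1 at each visit, complete data, compound symmetry with correlation ρ = 0.3, 0.5 or 0.7, and differences d of 0.2, 0.3 and 0.5 SD.

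**The plan's own figure.** The 152 can be neither reproduced nor refuted, since no effect size, SD or attrition rate is stated. Solved backwards (normal approximation), it corresponds to d = 0.4545 with no attrition: n = 2(1.960 + 0.842)²/0.4545² ≈ 76 per arm. It also corresponds to d = 0.5 (N = 126) with 17% attrition: 126/0.83 ≈ 152. So 0.5 SD is a reasonable upper case to display, but it is not a figure from the article.

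**Step 1: the omnibus interaction.** Let c be the profile of TEB-minus-TED differences over the three visits, centred on its mean. The F has 2 and 300 df and noncentrality λ = 2n · Σ(c/2)² / (1 − ρ). With d = 0.5 and ρ = 0.5:

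- TEB better at 2 months only, profile (0, 0.5, 0): Σc² = 0.1667, so λ = 152 × 0.04167/0.5 = 12.7.
- TEB better at both, (0, 0.5, 0.5): Σc² = 0.1667, so λ = 12.7.
- TED better at both, (0, −0.5, −0.5): Σc² = 0.1667, so λ = 12.7.
- TED better at 2 months, TEB better at 6 months, (0, −0.5, 0.5): Σc² = 0.5, so λ = 38.

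The first three cases have the same λ and therefore the same rejection rate. From the noncentral F, for ρ = 0.3 / 0.5 / 0.7:

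| Truth | 0.2 SD | 0.3 SD | 0.5 SD |
|---|---|---|---|
| No difference at any visit | 5% | 5% | 5% |
| TEB better at both; or TED better at both; or TEB better at one only | 17 / 23 / 35% | 34 / 46 / 69% | 77 / 90 / 99% |
| Reversal between 2 and 6 months | 44 / 59 / 82% | 80 / 92 / 99% | 100 / 100 / 100% |

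The interaction p-value therefore cannot separate the hypothesised pattern from its opposite or from a one-visit effect.

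**Step 2: testing the stated claim directly.** The TEB-minus-TED difference in change from baseline has standard error √(4(1 − ρ)/n). At ρ = 0.5 this is √(2/76) = 0.162, so d = 0.5 lies 3.08 standard errors from zero. Under compound symmetry the two visit contrasts correlate 0.5. Two rules were compared by simulation (accurate to about a percentage point), with TEB truly better at both visits:

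| Rule | Power at 0.3 SD | Power at 0.5 SD |
|---|---|---|
| Both contrasts favour TEB at two-sided 0.05 | 18 / 28 / 50% | 60 / 78 / 96% |
| Significant omnibus F, and both favour TEB at 0.025 | 11 / 18 / 38% | 48 / 67 / 92% |

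**Step 3: false both-visit claims.** If TEB is better at one visit only, the other contrast is null. It favours TEB by chance in at most 0.05/2 = 2.5% of trials under the direct rule, and 0.025/2 = 1.25% under Bonferroni. The simulated rates are about 2% and 1%. When TED is better at both visits, or the effect reverses, both rules give 0%. With no difference at all, the direct rule gives about 0.5%.

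**The case against.** A reader might infer that the planned test rejects 76–100% of the time whenever the hypothesis is false. The article does not support that. The hypothesis is also false when the arms are equal, and then the F rejects 5%. The high rates need a real difference of about 0.5 SD, a figure found nowhere in the article; at 0.2 SD the one-visit rate is 17–35%. Nor are they type I error. In each such case the arms truly differ and the F detects it. They become false claims only if a significant interaction is read as proof of TEB superiority at both visits, which the article does not say.

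Other points on that side also stand. The article says the model accounts for the interaction; it does not name the F as the decision rule. If the Bonferroni comparisons were between-arm and both had to favour TEB, false both-visit claims would be about 1%, stricter than the rule proposed here. Cohen's d, offered beside partial eta squared, is signed. The Discussion's two-tailed wording and the fourth objective fit a non-directional comparison. A full analysis plan, not shown, may name the contrasts.

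This does not remove the point. The article chose and published a between-group method, and that method does not address the claim in the Introduction. A two-tailed question about 2 and 6 months still needs signed, visit-specific contrasts. The strict reading of the post-hoc step is not stated, and it costs power.

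**Conclusion.** The point holds as a mismatch between hypothesis and named test, with a cheap improvement available. It is not an inflated error rate. A significant group × time interaction alone cannot support the Introduction's claim, because the F is equally likely to reject for TEB better at both visits, TED better at both, or TEB better at one. That equality follows from the noncentrality formula for equal differences under compound symmetry, whatever their size; the percentages rest on the assumed 76 per arm, effect sizes and correlations.

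Compared with the strictest reading of the plan, direct testing gains about 12/11/4 percentage points of power at 0.5 SD (60/78/96 minus 48/67/92) and 7/10/12 at 0.3 SD (18/28/50 minus 11/18/38). Separately, the Introduction (directional) and the Discussion (two-tailed, either arm may be superior) disagree on the hypothesis.

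**What to change.** In the Data analysis section and the Abstract:

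- Make the between-group analysis two signed 1-df contrasts from the same repeated-measures model: TEB minus TED change from baseline at 2 months and at 6 months, each two-sided at 0.05 with a 95% CI.
- Conclude the Introduction's hypothesis for an outcome only if both contrasts favour TEB. Since both must succeed, this claim needs no Bonferroni correction across visits.
- Keep Bonferroni for any claim based on a single visit, and report one-visit or TED-favouring results as such.
- Keep the omnibus F and partial eta squared as descriptive.
- Reconcile the directional wording of the Introduction with the two-tailed wording of the Discussion.

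The cost is wording only; data, model and software are unchanged. A significant omnibus F would no longer count as success. When only one visit truly differs, the false both-visit rate is about 2%, instead of the 1% that the strictest reading of the current plan would give.
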